## **9. Data Analysis – See Statistical Analysis Plan**

## **10. Safety And Dissemination**

Existing patients of UPMC will be part of this study. The study outcome (chlamydia and gonorrhea screening) is standard of care in the United States. Therefore there are no additional safety concerns to patients regarding the offer of a recognized preventive health screening using urine or swab collection for chlamydia and gonorrhea. Any concerns raised by the clinical staff at the practices during quarterly calls that are related to the conduct of this study will be reviewed by the Principal Investigator during monthly study meetings or at an earlier time if appropriate. Privacy of all patients will be

ensured by the use of an honest broker system that will protect the identity of each patient from the UPMC and the CDC investigators. Data transmitted to the CDC for analysis will be verified as de-identified before transmittal. Names and personal identifiers of physicians will not be collected, ensuring the privacy of the medical staff at each site. As the intervention is considered routine clinical practice (STD screening) we do not anticipate major safety issues during this study.

Findings of the project will be shared with the leadership at each office practice that participated in the study. Results will also be prepared for presentation at scientific meetings and for publication in peer-reviewed scientific journals.

## **11. Costs And Payments**

There are no costs or payments to patients or office practices as the study examines screening as part of standard clinical care.

## **12. Funding**

Funding for this investigator-initiated study is provided by the Centers for Disease Control and Prevention Foundation.

## **STOP STDs Statistical Analysis Plan (SAP)**

### **Randomization**

The primary care and obstetrics/gynecology practices were each randomized separately in a 1:1 ratio into intervention (alert) or control groups. Randomization was accomplished in the primary care practices by stratifying the practices according to urbanicity of the county where the practice was located (US Department of Agriculture Rural Urban Continuity Code (RUCC) = 1 versus  $\text{RUCC} \neq 1$ ) and by stratifying according to the percentage of the practice patient population of eligible women who were African-American (above the median for African-American women versus below the median for African-American women). Practices in each of the resulting four stratification groups were randomized using a random number generator to be intervention or control. In obstetrics/gynecology practices, randomization was done by stratifying on the basis of the percentage of the practice patient who were African-American only, due to all but 1 of the obstetrics/gynecology practices being in  $\text{RUCC} = 1$ .

### **Statistical Methods**

In this study, we will employ the following statistical methods to analyze the impact of a real-time alert system on chlamydia screening orders:

- **Baseline Characteristics:** Baseline characteristics will be summarized by study arm within each cohort (primary care and obstetrics/gynecology). Between-arm differences may be evaluated using 2-sided hypothesis tests ( $\alpha = 0.05$ ); however, P values will not be presented in Table 1. As a supplementary, sample size-independent measure,

standardized mean differences (SMDs) may also be calculated to aid interpretation of the magnitude of baseline differences and, if used, will be summarized briefly in the text.

- **Constrained Difference-in-Differences Mixed Effects Logistic Regression (Primary Approach):** We will estimate the intervention effect using a constrained difference-in-differences mixed-effects logistic regression model with a logit link. The model will include fixed effects for time period and the time-by-intervention interaction to compare pre-to-post changes between intervention and control practices. Random intercepts for practice (cluster) and patient will be included to account for within-cluster correlation and repeated encounters within patients. Models will be fit separately for primary care and obstetrics/gynecology practices. We will also report the intraclass correlation coefficient (ICC) to quantify the within-cluster correlation in the outcome, which is relevant for interpreting clustering and the precision of cluster-randomized estimates.
- **Small-Sample Inference for Cluster Randomized Designs:** Because the number of randomized clusters is fewer than 50, 95% confidence intervals and P values will be constructed using a t distribution with degrees of freedom (df) equal to  $K - p$ , where  $K$  is the number of clusters, and  $p$  is the number of cluster-level covariates included in the model.

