As most women infected with chlamydia and gonorrhea are asymptomatic, screening programs have been key strategic components of prevention efforts. Despite national screening recommendations, screening rates among young women have been suboptimal. Only 11% of 0.5 million sexually active women aged 15 years reported being tested for chlamydia in the prior year. Among women aged 15–21 years, chlamydia testing occurred very infrequently at visits to pediatricians (< 1%), and in only 28% of visits to a physician where a Pap test was performed. Several barriers to chlamydia screening have been identified. Taking a sexual history, particularly from younger patients is especially challenging. Providers may not recognize the need to screen at-risk patients. Many competing demands and priorities in an often brief clinical encounter can also be a barrier to STD screening, especially given the sensitive discussion about sexual behaviors that is necessary to identify those who should undergo screening. As such, novel strategies are urgently needed in order to overcome these barriers and increase screening rates for chlamydia and gonorrhea.

Interventions to increase chlamydia and gonorrhea screening directed to the providers have only been moderately effective. Clinical decision support systems, including clinician-facing electronic alerts that generate patient-specific recommendations, are widely used to promote best practices. However, a systematic review of point-of-care electronic alerts directed at physicians yielded only a modest effect, with a median care improvement of only 4.2%. The sheer number of alerts can desensitize a busy physician and cause alert fatigue, leading to ignoring or dismissing the alerts. Medical assistants generally do not receive alerts about clinical care and therefore might be less likely to face alert fatigue. Medical assistants might be more likely to interact with alerts

than other clinicians as they work under the direction of medical leadership of their practices. Further, an intervention directed at medical assistants during rooming in of patients could avoid burdening clinicians with additional tasks.

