## **2. Study Objectives**

The hypothesis of this study is that proportion of women ordered chlamydia screening will be higher in practices randomized to an electronic alert directed at medical assistants during rooming in of patients for their office visit than in practices without the electronic alert. Our primary objective is to compare the test order rates for *C. trachomatis* between practices randomized to the electronic alert compared to practices operating under routine care, separately for primary care practices and OBGYN practices. The secondary outcome will be to determine the test order rate in visits for reproductive care compared to visits for other medical reasons.

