## **7. Data Collection and Management**

The research informatics team at UPMC (CARE, see below) will capture pertinent clinical data in EMR for women attending in both the intervention and control practices. They will provide demographic and clinical information for data analyses that will include age, race, reason for visit, clinical services performed, chlamydia and gonorrhea test orders, and test results (if test results are available). All data will be de-identified prior to transfer to the investigators and to the CDC for data analyses.

The Center for Assistance in Research using eRecord (CARE) provides facilitated managed, compliant and secure access to the UPMC Electronic Health Record for researchers. CARE utilizes the EMRs and databases in use by UPMC. EMRs are currently deployed in both inpatient and outpatient clinics throughout the health system and provide a wealth of information for investigators. EpicCare is the EMR product in use in ambulatory clinics and outpatient offices affiliated with UPMC. The data contained in the EMRs are maintained behind a secure firewall on servers within the UPMC data center.

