### **Primary and Secondary Analyses**

The intervention consists of a real-time alert in the electronic medical record that will notify healthcare personnel when a non-pregnant woman aged 18-24 is eligible for chlamydia screening, defined as having no test order in the past year.

- **Primary Analysis:** The primary outcome will be the number of chlamydia screening orders placed during encounters. We will compare test order rates between intervention and control groups in primary care and obstetrics/gynecology practices.
- **Secondary Analysis:** The secondary analysis will evaluate the impact of the electronic alert on screening rates during reproductive health visits versus other visit types.

For each primary and secondary outcome, we will report the intervention effect as an odds ratio with a 95% confidence interval and P value (see Statistical Methods).

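### The primary model leaves out reason for visit, a covariate the trial already extracts and must code; if it strongly predicts ordering, the omission costs power and can make standard errors too small

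*Combined protocol and SAP*

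**What the plan says.** SAP, Statistical Methods, gives the fixed effects of the primary model: "The model will include fixed effects for time period and the time-by-intervention interaction". On the random part it says: "Random intercepts for practice (cluster) and patient will be included to account for within-cluster correlation and repeated encounters within patients". It lists no encounter-level or patient-level covariate, no practice-by-period term and no adjusted sensitivity model. Models are fitted separately for primary care and OBGYN.

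Protocol section 7 lists the data to be supplied for women in both arms, including "age, race, reason for visit, clinical services performed, chlamydia and gonorrhea test orders".

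Visit type appears only in the secondary question. Protocol section 2 aims to "determine the test order rate in visits for reproductive care compared to visits for other medical reasons". SAP, Primary and Secondary Analyses, will "evaluate the impact of the electronic alert on screening rates during reproductive health visits versus other visit types".

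On how ordering varies by kind of visit, protocol section 1 reports outside data on women aged 15 to 21: testing at under 1% of pediatrician visits, and "in only 28% of visits to a physician where a Pap test was performed".

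**The concern.** The outcome is observed per encounter, and a visit for contraception plausibly leads to a chlamydia order far more often than one for a sore throat. Both planned random intercepts are constant over time. They cannot absorb the difference between two visits by the same woman, or a change from pre to post in a practice's share of reproductive visits.

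Two things are at stake. In a logistic model, omitting a strong predictor pulls the estimated log odds ratio towards zero and lowers power. And with fewer than 50 practices over two cohorts, each tested at 0.025, chance shifts in visit mix in a few practices add variation to the pre-to-post contrast that the stated model does not represent.

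**Working it through.** **1. The plan's own figure.** Protocol section 8 gives 1882 per arm for 30% versus 35%, 90% power, two-sided 0.05. The usual two-proportion formula, n = [z(α/2)·√(2p̄(1−p̄)) + z(β)·√(p1(1−p1)+p2(1−p2))]² / (p2−p1)² with p̄ = 0.325, gives 1842. With the continuity correction, (n/4)·[1+√(1+4/(n·0.05))]² = 1882, an exact match. The planning odds ratio is (0.35/0.65)/(0.30/0.70) = 1.256, used below as the conditional alert effect.

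**2. Assumed inputs.** The documents give no visit mix, order rate by visit type, ICC or exact number of practices. Assumed: base order rate 30%; reproductive share 30% (20–40% in step 3); visit-type odds ratio 2, 4 or 8; K = 20 or 40 practices per cohort; m = 100, 200 or 500 encounters per practice and period; practice SD 0.4 on the logit scale; test at 0.025 with a t reference; 1000 runs per scenario. The patient intercept was left out and the practice SD held fixed.

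**3. Which drift matters.** Drift common to both arms goes into the period effect. A change d in the reproductive share in one arm only shifts that arm's order rate by d × (reproductive rate − other rate). With visit-type odds ratio 4 and a 20% share, the rates are 0.554 and 0.237. For d = 0.05 the shift is 0.05 × 0.317 = 0.0158, and the apparent odds ratio is (0.3158/0.6842)/(0.30/0.70) = 1.077. Over shares of 20–40%, a 5-point one-arm shift gives about 1.04 (visit-type odds ratio 2), 1.07–1.08 (4) or 1.10–1.12 (8), against a planned 1.256.

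**4. Power without drift, unadjusted → adjusted for visit type.**

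| K × m | OR 2 | OR 4 | OR 8 |
|---|---|---|---|
| 20 × 100 | 0.227 → 0.232 | 0.190 → 0.226 | 0.143 → 0.207 |
| 40 × 200 | 0.847 → 0.863 | 0.780 → 0.836 | 0.653 → 0.763 |
| 20 × 500 | 0.895 → 0.913 | 0.811 → 0.862 | 0.701 → 0.804 |

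The standard error does not fall. At 40 × 200 it goes from 0.067 to 0.070 (OR 4) and from 0.067 to 0.074 (OR 8). The mean log odds ratio rises by more, so the ratio of estimate to standard error goes from 0.210/0.067 = 3.13 to 0.230/0.070 = 3.29 (OR 4), and from 0.182/0.067 = 2.72 to 0.227/0.074 = 3.07 (OR 8).

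**5. Chance drift by practice, unrelated to arm.** Drift SD is 0.3 on the logit of the share, about 0.3 × 0.30 × 0.70 = 0.063, or 6 points near a 30% share. Null rejection at nominal 0.025, unadjusted / adjusted:

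| K × m | OR 2 | OR 4 | OR 8 |
|---|---|---|---|
| 20 × 100 | 0.007 / 0.010 | 0.020 / 0.019 | 0.023 / 0.013 |
| 40 × 200 | 0.021 / 0.021 | 0.034 / 0.020 | 0.042 / 0.019 |
| 20 × 500 | 0.016 / 0.011 | 0.033 / 0.014 | 0.068 / 0.014 |

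The unadjusted null estimate stays centred (mean log odds ratio −0.003 to 0.005). Its standard error is the problem. At 20 × 500 the model reports 0.061 against an empirical SD of 0.073 (OR 4) and 0.082 (OR 8), so it is 1 − 0.061/0.073 = 16% and 1 − 0.061/0.082 = 26% too small. Simulation error matters here: with 1000 runs the standard error of a true 0.025 is √(0.025 × 0.975/1000) = 0.005. A rate of 0.033 is therefore not clearly above nominal, whereas 0.068 is.

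**6. Other assumed settings.**
- 20 practices, 300 encounters per practice-period, 25% reproductive visits: gains of about 0–2 points at order rates 28%/20%, 5–7 at 50%/20% and 9–13 at 50%/12%. The visit-type odds ratios are (0.28/0.72)/(0.20/0.80) = 1.6, then 4.0, then 1/(0.12/0.88) = 7.3. With drift SD 0.3, unadjusted null rejection was 5–7% and adjusted about 1.5%.
- 20 practices, 200 encounters, a larger alert effect (log odds ratio 0.35) and cluster-robust errors: 69% → 72% at 50%/20% without drift; at 50%/12%, 53% → 64% with 3-point drift and 48% → 65% with 5-point drift. Null rejection was 2.2–2.4%, so the inflation belongs to model-based errors. Adjusting for age alone, at the 40% versus 47% in protocol section 8, moved power from 83.0% to 83.2%.

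**The case against.** The strongest reply is that an unadjusted randomized comparison is valid and answers the pragmatic objective directly, that the effect by visit type is already a secondary analysis, and that every gain above rests on inputs the documents do not contain. The first two parts stand, and they make this an improvement, not the correction of an invalid analysis. The third means the size is a range: at a visit-type odds ratio of 2 there is almost nothing to gain.

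Three stronger readings are tempting, and the documents do not support them:

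- A reader might infer that the protocol itself calls visit reason a strong driver of ordering. It does not. The section 1 figures come from outside data in women aged 15 to 21, and they set a provider specialty that is not in this trial against a service performed. They and the secondary objective make a strong association plausible but do not measure it.
- A reader might infer that adjustment tightens the estimate. Without drift, the standard error of the log odds ratio rises slightly. The gain is in power, and the adjusted odds ratio is a different, conditional quantity.
- A reader might infer that visit-mix drift biases the alert effect. Common drift is absorbed by the period term, and under randomization differential drift is chance noise. It would be systematic only if the alert or the staff training changed the visit mix or its coding.

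It is also fair to say that the understated standard errors reflect the absence of a practice-by-period term; adjusting for visit reason removes only the part due to visit mix. The simulations omit the patient intercept and assume one alert effect for all visit types, so the gain under the full SAP model is untested. Finally, section 7 does not say when reason for visit is recorded. If it is coded after the alert, it is post-randomization and adjusting for it is not automatically safe.

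**Conclusion.** The point holds as a recommendation on power and robustness. The primary model omits an available covariate that must be coded anyway. Under the assumed inputs the cost is about 0–2 power points for a weak association and roughly 5–13 for visit-type odds ratios of about 4 to 8. A few scenarios fall outside that range: 3 to 4 points in two of the settings at odds ratio 4, and up to 17 with strong drift. Adjustment lowered power in none.

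Chance drift by practice can also take null rejection to about 3–7% at a nominal 2.5%, when the association is strong, practices contribute many encounters and standard errors are model-based. With 20 practices and 100 encounters per period there was no inflation.

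The benefit is likely to be smaller in OBGYN if most visits there are reproductive. Nothing here makes the unadjusted estimate biased or the planned analysis invalid.

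**What to change.** In SAP, Statistical Methods:

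- Add visit reason (reproductive versus other) as a fixed effect in each cohort's primary model. Take it from a reason recorded before the alert opens, and fix the grouping before any outcome analysis by arm.
- Keep the currently stated model as a prespecified sensitivity analysis. If no pre-alert reason can be extracted, keep the stated model as primary and make the adjusted one the sensitivity analysis.
- State that the odds ratio is then conditional on visit reason as well as on practice and patient.
- Age at the encounter may be added, but expect a negligible gain.

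The K − p degrees of freedom do not change, because p counts only cluster-level covariates. The cost is a few lines of SAP text, a coding step the secondary analysis already needs, and a check with the informatics team on when reason for visit is entered. Whether a pre-alert field is already in the extract is not stated and has to be confirmed.

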## **8. Sample Size Calculation**

Assuming that the screening rate in the usual care group is 30% and in the opt-out group it will be 35%, a study recruiting 1882 patients in the usual care group and 1882 patients in the opt-out group will result in 90% power to detect a significant difference in the proportion of women screened for chlamydia at a two sided .05 significance level. As such we propose to recruit at least 2000 patients in the opt-out group and 2000 patients in the usual care group.

If the baseline screening is closer to the 2011-2012 average commercial (non-Medicaid) screening rate of sexually active women (40% in 16-20 year olds and 47% in 21-24 year olds) we would need to enroll 898 women ages 16-20 and 228 women ages 21-24 in order to demonstrate a 20% increase in screening at 90% power. The proposed study would provide enough power to examine both of these age groups.

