## **Significance Levels**

The familywise significance level will be set at  $\alpha = 0.05$  (2-sided). Because the primary endpoint will be evaluated in 2 parallel cohorts (primary care and obstetrics/gynecology practices), we will apply a Bonferroni correction, using  $\alpha = 0.025$  per cohort-specific primary comparison. For secondary outcomes, hypothesis tests will be interpreted using a 2-sided significance threshold of  $\alpha = 0.05$  unless otherwise specified.

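### The primary model has no practice-by-period random effect, so its standard error is too small whenever practices drift differently from pre to post

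*Combined protocol and SAP*

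**What the plan says.** The SAP, under Statistical Methods, sets out a constrained difference-in-differences logistic model, fitted separately in primary care and in obstetrics/gynecology. On the fixed effects: "The model will include fixed effects for time period and the time-by-intervention interaction to compare pre-to-post changes between intervention and control practices". On the random effects: "Random intercepts for practice (cluster) and patient will be included to account for within-cluster correlation and repeated encounters within patients".

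The small-sample provision in the same section is worded "Because the number of randomized clusters is fewer than 50", and intervals and P values are then "constructed using a t distribution with degrees of freedom (df) equal to" K - p. On correlation, the plan says: "We will also report the intraclass correlation coefficient (ICC) to quantify the within-cluster correlation in the outcome". Only one such coefficient is mentioned.

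Under Significance Levels, "we will apply a Bonferroni correction" gives each cohort's primary test a two-sided 0.025. Neither the SAP nor the protocol mentions a practice-by-period term, a random period slope, a cluster-robust variance, a permutation test or a practice-level sensitivity analysis.

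**The concern.** The estimand is a difference in change between randomised practices. A time-constant practice intercept describes stable differences in level, and these largely cancel from a pre-to-post contrast. The error that remains at the level of randomisation is how differently practices change for reasons other than the alert, such as staff turnover, local initiatives or case mix. The model has no term for this.

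The other parts of the model do not supply it. The patient intercept is also constant over time and independent between patients, so it cannot represent a shift shared by all patients of one practice in one period. The t reference changes the critical value and leaves the standard error alone. With a single ICC reported, drift would not be visible in the output either.

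At stake is the primary test in both cohorts. If drift exists, the error favours declaring a difference and weakens the Bonferroni protection at 0.025.

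**Working it through.** **What the documents supply.** They state no standard error or type I error for the primary model, so there is no such figure to reproduce. The one planning figure is 1882 per group (protocol section 8; 30% vs 35%, 90% power, "at a two sided .05 significance level"). The two-proportion formula with continuity correction returns 1882, and without it 1842. It is an individual-level calculation with no cluster or period term, so it yields no ICC or between-period correlation.

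**Inputs.** From the documents: two periods, 1:1 allocation, K below 50, alpha 0.025 per cohort, at least 2000 patients per group, and a 30% usual-care rate. Assumed: K = 24; p = 1 in K - p; order rate π₀ of 15% or 30%; latent-scale ICC 0.01 to 0.05; between-period correlation (CAC) 0.8 to 1; m encounters per practice-period. Dividing 2000 by 12 practices per arm gives about 167. That is only a guide to m, because 2000 is a minimum and counts patients.

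**Approximation on practice-period logits.**
- Sampling variance v = 1/[m π₀(1 - π₀)].
- Total practice variance τ² = ICC/(1 - ICC) × π²/3, split into a constant part s = CAC × τ² and a practice-by-period part g = (1 - CAC) × τ².
- The intercept-only model fits practice variance of about σ² = s + g/2 and weights the pre-period by r = σ²/(σ² + v).
- Model SE² = (4/K)(σ² + v)(1 - r²).
- True SD² = (4/K)[(τ² + v)(1 + r²) - 2rs].
- Rejection = 2Φ(-t × SE/SD), with t = 2.398 (0.9875 quantile, 23 df).

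**Worked case: 15%, ICC 0.05, CAC 0.8, m = 500.** v = 1/(500 × 0.1275) = 0.0157; τ² = 0.1732; s = 0.1385; g = 0.0346; σ² = 0.1558; r = 0.9085. Model SE = √[(4/24)(0.1715)(0.1746)] = 0.071. True SD = √[(4/24)(0.1888 × 1.8254 - 2 × 0.9085 × 0.1385)] = 0.125. Rejection = 2Φ(-2.398 × 0.567) = 17.4%. As m grows the model SE tends to zero, while the true SD has a floor of √(8g/K) = 0.107.

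Other CAC values, same case: 1.6% at CAC 1.0 and 9.4% at 0.9. Simulated null trials of the practice-intercept logistic model (300 per scenario) gave 1.7%, 9.3% and 17.7% at CAC 1.0, 0.9 and 0.8. At 0.8 the mean SE was 0.070 against a true SD of 0.123.

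**Cells near the planned minimum (K = 24, m = 167), rejection at nominal 2.5%:**

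| ICC | 15%, CAC 0.9 | 15%, CAC 0.8 | 30%, CAC 0.9 | 30%, CAC 0.8 |
|---|---|---|---|---|
| 0.01 | 1.9% | 2.2% | 2.2% | 2.7% |
| 0.02 | 2.3% | 3.0% | 2.9% | 4.2% |
| 0.05 | 3.7% | 6.2% | 5.5% | 10.0% |

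**Repeated encounters.** The figures above treat encounters as independent. Multiplying v by an assumed patient design effect of 1.5 or 2 lowers the 17.4% case to 12.0% or 9.1%.

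**Separate simulation at a 30% rate** (1500 runs, restricted maximum likelihood on empirical logits, K - 1 df). The last column adds a practice-by-period intercept:

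| K, m, ICC | CAC | As planned | With added term |
|---|---|---|---|
| 20, 200, 0.05 | 1.0 | 1.3% | 1.3% |
| 20, 200, 0.05 | 0.9 | 5.5% | 2.4% |
| 20, 200, 0.05 | 0.8 | 9.2% | 2.9% |
| 40, 500, 0.05 | 0.9 | 14.6% | 2.2% |
| 20, 200, 0.02 | 0.9 | 2.3% | 1.5% |

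Fitting the first three as practice-intercept logistic models (600 runs) gave 1.0%, 7.0% and 10.5%.

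**The case against.** A reader might infer that the planned standard error is too small as a matter of fact, and that the false-positive rate is therefore inflated. The documents do not support that. If all practices move together on the logit scale apart from the alert, the model is adequate and the test is slightly conservative (1.0% to 2.0% at CAC 1 across the simulations). With a low ICC and small cells, inflation is negligible even with drift. Nothing in the documents shows that drift is present or how large it is.

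A reader might also take 17%, or the 30% obtained with 1000 encounters per practice-period, as the expected error rate. These are upper-end scenarios. With 12 practices per arm, 500 to 1000 encounters per cell means 6,000 to 12,000 encounters per arm per period, well above the stated minimum of 2000 patients per group. Larger cells are possible, since the minimum counts patients and the analysis is of encounters, but the documents do not establish them. The calculations also omit the patient intercept and use equal practice sizes, and the first of these overstates the inflation.

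Finally, the plan does model clustering and does use a small-sample reference distribution. All of this stands as a limit on size. It does not change the direction: the missing variance can only be zero or positive, and no other part of the plan supplies it.

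**Conclusion.** The concern holds in conditional form. The plan targets a pre-to-post contrast with a model that fixes practice-specific change at zero. If practices drift differently, the primary intervals and P values in both cohorts are anti-conservative, and the K - p reference does not correct this.

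Confidence is high on the omission and its direction, and lower on its size. At cells near the planned minimum, the result runs from no inflation to about four times nominal (10% against 2.5%). At 500 encounters and ICC 0.05 it is about 9% to 17% before allowing for repeated encounters. These ranges rest on assumed K, ICC, between-period correlation, order rate and cell size. Because the correction is one model term, it is worth making without waiting to learn how large the drift is.

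**What to change.** Replace the random-effects sentence in the SAP with: *Random intercepts for practice, practice-by-period and patient will be included.* Keep degrees of freedom based on the number of practices in the cohort being analysed, and report within-period and between-period ICCs.

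Prespecify that this model governs the primary conclusion even if the practice-by-period variance is estimated near zero. Dropping the term when its estimate is zero would let the data choose the model and would restore the present weakness where few practices make zero estimates likely. As a sensitivity analysis, add a practice-level comparison of pre-to-post change, or a permutation test within the randomisation strata. A random period slope should not be treated as interchangeable: with 0/1 period coding it implies unequal pre and post variances unless the covariance is constrained.

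Cost: wider intervals, slight conservatism if there is no drift (1.1% to 1.9% at nominal 2.5% in the 30%-rate simulation), and possible boundary variance estimates with few practices. With drift, the added term brought rejection to 1.5% to 3.1% in that simulation. Those checks used empirical logits without a patient effect. The full logistic model with all three intercepts was not fitted, so its behaviour at the actual number of practices should be simulated before the SAP is finalised.

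### The two primary odds ratios are tested at 0.025 but reported with 95% confidence intervals, so an interval can exclude 1 when its test has failed.

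*Combined protocol and SAP*

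**What the plan says.** Three parts of the SAP bear on this.

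- **Significance Levels.** "The familywise significance level will be set at" 0.05, two-sided. The section continues: "Because the primary endpoint will be evaluated in 2 parallel cohorts (primary care and obstetrics/gynecology practices), we will apply a Bonferroni correction, using" 0.025 "per cohort-specific primary comparison". Secondary outcomes keep a two-sided 0.05.
- **Primary and Secondary Analyses.** "For each primary and secondary outcome, we will report the intervention effect as an odds ratio with a 95% confidence interval and P value". One confidence level thus serves both tiers.
- **Statistical Methods, small-sample inference item.** "95% confidence intervals and P values will be constructed using a t distribution with degrees of freedom (df) equal to" K − p. Here K is the number of clusters and p "is the number of cluster-level covariates included in the model". The same rule serves the interval and the P value. K is described only as below 50, and no count of practices is given for either cohort.

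No section plans a 97.5% interval for the primary comparisons, and none labels the 95% intervals as unadjusted for multiplicity.

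**The concern.** A 95% interval is the counterpart of a two-sided test at 0.05. The primary tests are held to 0.025, and the counterpart of that test is a 97.5% interval. The SAP separates primary from secondary outcomes when it sets thresholds, but not when it sets interval levels.

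The two cohort-specific odds ratios are the trial's main results, and many readers judge such a result by whether its interval excludes 1. If one cohort lands between the two thresholds, the report would show an interval that suggests an effect beside a test that, by the SAP's own rule, has not shown one. The plan does not say how that result should be presented.

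The degrees-of-freedom rule raises a smaller and separate question. If p counts covariates only, the intercept is not deducted, and the reference distribution may have slightly too many degrees of freedom in a cohort with few practices.

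**Working it through.** **Inputs.** From Significance Levels: familywise level 0.05 two-sided, two primary comparisons, 0.025 each. From Statistical Methods: 95% intervals, a t reference with df = K − p, and K below 50. Assumed here, because the documents do not say: K per cohort from 8 to 49, and p = 1, so df = K − 1.

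**1. The plan's own figure.** 0.05 / 2 = 0.025, and 0.025 + 0.025 = 0.05. The Bonferroni split is correct.

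**2. Where interval and test disagree.** The 95% interval excludes 1 when |t| exceeds t(0.975, df). The primary test succeeds when |t| exceeds t(0.9875, df). Between the two values, the interval excludes 1 and the test fails.

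| K (assumed) | df = K − 1 | t(0.975) | t(0.9875) | Ratio |
|---|---|---|---|---|
| 8 | 7 | 2.365 | 2.841 | 1.20 |
| 10 | 9 | 2.262 | 2.685 | 1.19 |
| 12 | 11 | 2.201 | 2.593 | 1.18 |
| 20 | 19 | 2.093 | 2.433 | 1.16 |
| 30 | 29 | 2.045 | 2.364 | 1.16 |
| 49 | 48 | 2.011 | 2.314 | 1.15 |

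The ratio is the width of the matched 97.5% interval relative to the planned 95% interval on the log-odds scale: 20% wider at K = 8, falling to 15% at K = 49. Every row has a zone of disagreement. On the P scale it is always 0.025 to 0.05.

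**3. Illustration (assumed values).** Take K = 20, df = 19, odds ratio 1.25 and t = 2.25. Then ln(1.25) = 0.2231 and SE = 0.2231 / 2.25 = 0.0992.

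- P = 0.036, which exceeds 0.025, so the primary test fails.
- 95% interval: exp(0.2231 ± 2.093 × 0.0992) = 1.016 to 1.538, which excludes 1.
- 97.5% interval: exp(0.2231 ± 2.433 × 0.0992) = 0.982 to 1.591, which includes 1.

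**4. Does the df rule contribute?** Repeat step 3 with one fewer degree of freedom (18). P becomes 0.037, the 95% interval 1.015 to 1.540 and the 97.5% interval 0.981 to 1.593. The disagreement is unchanged. One df serves both interval and P value, so the df rule cannot make them diverge. Only the choice of 95% against 0.025 does that.

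**5. Size of the df point alone.** Suppose K − 2 is the right reference, as for a practice-level contrast of two arms, and the test is run at nominal 0.025 with K − 1. Its actual level is 2 × P(t with K − 2 df > t(0.9875, K − 1)):

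- K = 8: 0.0295
- K = 10: 0.0277
- K = 12: 0.0268
- K = 20: 0.0256
- K = 49: 0.0251

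**The case against.** The strongest reply is that nothing in the plan's decision-making goes wrong. The SAP names the threshold for each primary comparison, reports a P value beside every interval, and nowhere makes the 95% interval the criterion. An unadjusted 95% interval beside a multiplicity-adjusted threshold is a common reporting convention. This stands as a defence of the test, and it makes the point one of reporting. It does not remove the mismatch, because the SAP does not say that the intervals are unadjusted.

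A reader might go further in three ways that the documents do not support.

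- **That familywise error is inflated.** Judging two independent cohorts by whether a 95% interval excludes 1 would give 1 − 0.95² = 9.75%. That is the error rate of a rule the SAP does not adopt, and it assumes independence. The stated rule keeps the familywise rate at or below 5%, subject to the small df question.
- **That the df rule helps cause the disagreement.** Step 4 of the working shows that it cannot.
- **That the interval is about 18% too narrow for the stated test.** That figure, at an assumed K of 10, is 1 − 2.262/2.752. It sets a 95% interval at K − 1 against a 97.5% interval at K − 2, which mixes two issues. Against the stated test it is 1 − 2.262/2.685, about 16%.

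On df, it is fair to object that the word covariates may have been meant loosely, to include every cluster-level parameter. The intervention also enters this constrained model only through its interaction with time, so K − 2 is not plainly the exact reference. Because the models are fitted separately by cohort, the ordinary reading already makes K cohort-specific. What remains is an unclear definition rather than a demonstrated error.

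**Conclusion.** The mismatch is real and follows from the text alone. Primary comparisons are tested at 0.025 and reported with 95% intervals, so any primary P value between 0.025 and 0.05 pairs a failed test with an interval that excludes 1. This holds whatever the number of practices. Only its width depends on the assumed K and p: matched intervals are about 20% wider at K = 8 and 15% wider at K = 49. It is an inconsistency of reporting and interpretation, and the planned test and its error control are unaffected. It still merits correction before results are reported, because it touches the trial's main estimates.

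The df point is separate, minor and conditional. It holds on a literal reading of p and if K − 2 is the right reference. It could matter slightly in a cohort of about 8 to 12 practices and is negligible from about 20 upwards. The documents do not show which case applies.

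**What to change.** In the SAP, under Statistical Methods and under Primary and Secondary Analyses, specify 97.5% confidence intervals for the two cohort-specific primary odds ratios and keep 95% for secondary outcomes. If 95% intervals are also wanted for the primary effects, for instance for comparison with other studies, label them as not adjusted for multiplicity.

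In the same edit, define the df rule fully: p counts all cluster-level parameters, including the intercept and the intervention term, and K is the number of practices in that cohort's model. State K for each cohort.

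The cost is SAP wording. The primary intervals become about 15% to 20% wider on the log-odds scale. Deducting the intercept adds 4.5% to the 0.025 critical value at K = 8 and under 0.5% at K = 20. No change to design or data is needed.
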